## Abstract

**Background:**

Exercise intolerance is a common finding in heart failure that generates a vicious cycle in which the individual starts to limit his activities even more due to progressive fatigue. Regular physical exercise can increase the cardiopulmonary exercise capacity of these individuals. A new approach to physical exercise, known as functional training, could improve the oxygen consumption and quality of life of patients with heart failure; however, there is no information about the effect of this modality of exercise in this patient population. This randomized trial will compare the effects of 36 sessions of functional training versus strength training in heart failure patients.

**Methods:**

This randomized parallel-design examiner-blinded clinical trial includes individuals of both sexes aged ≥40 years receiving regular follow-up at a single academic hospital. Subjects will be randomly allocated to an intervention group (for 12-week functional training) or an active comparator group (for 12-week strength training). The primary outcomes will be the difference from baseline to the 3-month time point in peak oxygen consumption on cardiopulmonary exercise testing and quality of life assessed by the Minnesota Living with Heart Failure Questionnaire. Secondary outcome measures will include functionality assessed by the Duke Activity Status Index and gait speed test; peripheral and inspiratory muscular strength, assessed by hand grip and manovacuometry testing, respectively; endothelial function by brachial artery flow-mediated dilation; lean body mass by arm muscle circumference; and participant adherence to the exercise programs classified as a percentage of the prescribed exercise dose.

**Discussion:**

The functional training program aims to improve the functional capacity of the individual using exercises that relate to his specific physical activity transferring gains effectively to one’s daily life. In this context, we believe that that functional training can increase the cardiopulmonary exercise capacity and quality of life of patients with heart failure. The trial has been recruiting patients since October 2017.

**Trial registration:**

NCT03321682. Registered on October 26, 2017.

## Background

Exercise intolerance is a common finding in heart failure (HF) that generates a vicious cycle in which the individual starts to limit his activities even further due to progressive fatigue [1]. The mechanisms underlying exercise intolerance are generally considered multifactorial and include endothelial dysfunction. In patients with HF, improved endothelial dependent dilation as a result of exercise training is associated with increased exercise capacity, even in the absence of improved cardiac output [2]. Patients with HF, even when stable and compensated, experience a decline in functional capacity associated with a lower quality of life [3, 4]. Recent evidence suggests that exercise-based cardiac rehabilitation improves quality of life and functional capacity [5]. Despite the known benefits of physical training for patients with HF, the rates of adherence with recommended exercise are low, potentially limiting its ability to improve clinical outcomes [6].

In fact, a loss of strength and muscle mass, known as sarcopenia, is highly prevalent in this population and constitutes an important determinant of functional independence, hospitalization rates, and quality of life [7]. Patients with HF have a 30% decreased ability to perform activities of daily living (ADLs) compared to healthy individuals, which has been attributed to reduced muscle mass and decreased oxygen consumption (VO_2_) [8]. In this context, strength training increases muscle torque and endurance, functional independence, and quality of life, reducing the morbidity of individuals with and those without cardiovascular disease [9]. The lower overload to the cardiorespiratory system related to strength training may be a safe and comfortable alternative for exercise prescription to patients with HF [10]. Recent meta-analyses have shown a significant increase in peak VO_2_ in patients with HF as a clinical outcome of strength training [11, 12].

However, ADLs require a combination of endurance and strength, and aerobic training alone does not improve muscle strength [13]. In addition, traditional resistance/strength training does not ideally represent the movements performed during ADLs since it does not include exercises using coordinated and multiplanar movement patterns or incorporate multiple joints and dynamic tasks [14].

Functional training may be a potential effective nonpharmacological therapeutic intervention for patients with HF. Articles related to functional training published to date did not include peak VO_2_ as an outcome, which makes this intervention innovative for patients with HF. Studies including functional training basically focused on assessing functionality in an elderly population in terms of walking capacity [15] and mobility [16]. This exercise method consists of integrated movements of the body in several planes that involve joint acceleration and deceleration, stabilization, strength, and neuromuscular efficiency (Fig. 1).

**Fig. 1 Fig1:**
[figure not shown]
Examples of functional exercises. Legend: 1, run on trampoline; 2 (a, b), Swiss ball wall squat; 3, overhead press with dumbbells; 4 (a, b), plank and variation; 5, squat on rigid balance board; 6 (a, b), oblique twist with elastic band; 7, agility on ladder drills; 8 (a, b), reverse plank

The method aims to improve the functional capacity of the individual using exercises that relate to his specific physical activity, effectively transferring gains to one’s daily life [14, 17]. In fact, functional training, sometimes called neuromotor exercise training, is a recommendation of the American College of Sports Medicine for apparently healthy adults of all ages [18]. Functional training could improve peak VO_2_ since it also includes an aerobic component. However, some aspects such as volume, performance patterns, and progression remain unknown. Additionally, the effectiveness of exercise training in chronic diseases has not been established [14]. The choice of the strength group as an active comparator group was because this type of training does not increase peak VO_2_ in the same magnitude as exercises with a larger cardiopulmonary component, as we expect in functional training. The primary objective of the present study is to compare the effects of functional training versus strength training on the cardiopulmonary exercise capacity and quality of life of patients with HF. Secondary objectives are to evaluate the: (1) effects of functional training versus strength training on functionality, muscle strength, endothelial function, and lean body mass; (2) adherence of participants to both physical training protocols; and (3) safety of a functional training program.

## Methods/design

### Study setting

This randomized parallel-design 1:1 ratio allocation examiner-blinded clinical trial is conducted at the Hospital de Clínicas de Porto Alegre (HCPA), a tertiary hospital in the city of Porto Alegre, Southern Brazil. The study was approved by the facility’s institutional review board on August 8, 2017 (protocol no. 20170291). The study protocol adheres to the SPIRIT 2013 recommendations [19] (Additional file 1). The World Health Organization Trial Registration Dataset is provided herein (Additional file 2). Written informed consent is obtained from all patients before participation (Additional file 3).

### Eligibility criteria

The study’s inclusion and exclusion criteria are defined below.

#### Inclusion criteria

Age equal to or older than 40 years.Clinically stable HF (ischemic and non-ischemic) for at least 3 months before randomization and diagnosed according to clinical records.New York Heart Association (NYHA) functional class II–III with slight to marked limitation of physical activity, respectively [20].Left ventricular ejection fraction (LVEF) equal to or less than 45%.Optimized pharmacological treatment [20].

#### Exclusion criteria

Enrollment in another clinical trial involving physical training protocols.Regular practice of physical exercise of more than 150 min per week [21] in the last 3 months.Decompensated HF.Acute myocardial infarction and/or cardiac surgery for less than 6 months.Severe valvular heart diseases and/or uncontrolled cardiac arrhythmias.Asymmetric septal hypertrophic cardiomyopathy with a dynamic obstruction in the outflow pathway.Musculoskeletal disorders limiting completion of the protocol exercise program.Impaired cognitive status that compromises the understanding of the steps and completion of the study protocol.

### Intervention

The participants are randomly allocated to a functional training program or a strength training program, each lasting 3 months. The exercise sessions are completed at the Center of Clinical Research at the HCPA. The patients perform the exercise training three times/week for a total of 36 sessions. Both physical exercise training programs are performed under the supervision of a physiotherapist who specialized in sports sciences. The exercises are performed individually or in pairs. Resting heart rate (HR) and blood pressure are measured with a validated digital automatic sphygmomanometer before and after each training session. The first two training sessions are earmarked for patients to become familiar with the exercises.

Each training session lasts approximately 50–60 min, consisting of an initial warm-up of 5 min, 35–45 min of functional or strength exercises, and 10 min of stretching and cool-down (Table 1).

**Table 1 Tab1:** Phases of the sections and collection of exercises performed in training protocols

Functional Training Session	Strength Training Session	Time
***Warm-up:*** Run on the trampoline	***Warm-up:*** Stationary gait and calisthenics exercises	5 min
***Functional exercises:*** Core strength Agility and balance Knee and hip dominance Vertical pressure Horizontal pressure Horizontal and vertical pulling	***Strength exercises:*** Shoulder abduction Triceps extension Biceps curls, bench press Abdominals, calf raises Leg extension, seated leg curl Leg press and leg abduction	35–45 min
***Cool-down:*** Stretching exercises for lower limbs, upper limbs, and spine	***Cool-down:*** Stretching exercises for lower limbs, upper limbs, and spine	10 min

#### Functional training

Each phase of functional training includes a total of 10–12 different exercises. Prescribed movements consist of multi-joint exercises emphasizing major muscle groups and ADLs like sitting, standing up, pushing, and pulling. Unstable surfaces, cones, ladder drills, elastic bands, kettlebells, dumbbells, steps, and Swiss balls are used in the training. Exercise intensity is self-paced, although the participants are encouraged by the physical therapist to exercise at high performance (time and number of repetitions) and progressively increase its performance or the difficulty of each exercise. A rest period between the series is determined by the time required for proper patient positioning and breath recovery. Indeed, the exercises are adjusted for each session depending on changes in functional and health status. The sequence of the functional exercises is designed to alternate strength exercises with agility training or strength exercises with aerobic conditioning as well as arm exercises with leg exercises always grouped in pairs or every three exercises. Running on the trampoline is performed as the warm-up and repeated at the end of the session before stretching exercises (Table 2).

**Table 2 Tab2:** Functional training protocol: exercises and periodization model

**Phase 1** − 4 weeks-	Run on trampoline	–	3 sets of 40 s
	Sit to stand (body weight)	–	2 sets of 30 s
	Biceps curls with elastic band	–	2 sets of 10–12 rep
	Suicide	–	2 sets of 30 s
	Sumo squat (with 4-kg kettlebell)	–	2 sets of 30 s
	Standing band row	–	2 sets of 10–12 rep
	Low step up (10-cm height)	–	2 sets of 40 s
	Lateral band walk	–	2 sets of 30 s
	Basic crunch	–	2 sets of 10–20 s
	Hip adductor ball squeeze	–	2 sets of 30 s
	Frontal plank	–	2 sets of 15–20 rep
	Run on trampoline	–	3 sets of 40 s
**Phase 2** − 4 weeks-	Run on trampoline	–	3 sets of 50 s
	Squat on rigid balance board	–	1 set of 30 s for each side
	Oblique twist with elastic band	–	1 set of 10–12 rep for each side
	Side to side run with cones	–	1 to 2 sets of 30 s
	Kettlebell high pull (4 kg)	–	2 sets of 10–12 rep
	Lunges (body weight)	–	1 to 2 sets of 30 s for each leg
	Low step up (10-cm height)	–	2 sets of 50 s
	Basic crunch	–	2 sets of 15–20 rep
	Reverse crunch	–	1 to 2 sets of 15–20 rep
	Swiss ball hip raise	–	1 set of 10 rep
	Frontal plank	–	1 to 2 sets of 10–20 s
	Lateral plank	–	1 set of 10–20 s
	Run on trampoline	–	3 sets of 50 s
**Phase 3** − 4 weeks-	Run on trampoline	–	3 sets of 60 s
	Swiss ball wall squat	–	2 sets of 30 s
	Triceps bench dips	–	2 sets of 10–12 rep
	Step up (20-cm height)	–	1 set of 30 s for each leg
	Agility on ladder drills	–	1 to 2 sets of 30 s
	Dumbbell shoulder press Swiss ball (2 kg)	–	2 sets of 10–12 rep
	Walking lunge (body weight)	–	1 to 2 sets of 30 s
	Basic crunch	–	2 sets of 15–20 rep
	Reverse crunch	–	1 to 2 sets of 15–20 rep
	Hamstring curl with a Swiss ball	–	2 sets of 10–12 rep
	Reverse plank with leg lift	–	4 sets of 3 s for each leg
	Plank with leg lift	–	1 set of 10 s for each leg
	Run on trampoline	–	3 sets of 60 s

*Sec* second, *Rep* repetition

#### Strength training

The strength training follows the recommendations for resistance training in individuals with cardiovascular disease by the American Heart Association [9]. The exercise protocol involves large muscle groups alternating their execution between the upper and lower limbs. Free weights (dumbbells, barbells, and ankle weights) and weight machines are used in the training. Two sets of 8–12 repetitions for the upper limbs and 12–15 repetitions for lower limbs are performed. The participants are encouraged by the physical therapist to perform a higher number of repetitions. The first two sessions are designed to determine the load of each exercise using the Borg scale (effort target of 3–4) and adapt the participant to the training. The progression of the exercises occurs at 4-week intervals.

#### Criteria for discontinuation and safety interventions

A participant may be discontinued from the study at the investigator’s discretion for safety reasons. For any study subjects, an incident cardiovascular event, hospitalization, or severe health event during the intervention period are considered criteria to discontinue study participation. If typical thoracic pain, disabling dyspnea, and/or exercise-related syncope occur during the training session, the exercise intervention will be interrupted. Trained nursing staff at the clinical research center will provide clinical assessment and event-directed interventions accordingly. If necessary, immediate transfer to the hospital’s emergency department will be performed.

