### Outcomes

The outcomes are assessed at baseline and after the provision of written informed consent but before allocation to one of the study groups. At the end of the 12-week period, the subject will be re-evaluated (Fig. 2).

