### Sample size

Our sample size calculation was based on Feiereisen et al., who enrolled subjects with HF with reduced ejection fraction to assess the effect of strength in comparison with aerobic and combined aerobic-strength training on their peak VO_2_ [31]. Considering a power of 80%, a significance level of 5% and an effect size of 0.2 for the peak VO_2_, a total sample size of 32 subjects was estimated, including 16 in each study group. To account for a 20% estimated participant loss or refusal rate, we defined that 19 patients should be enrolled in each group, totalizing 38 subjects.

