### Data collection

Standard operating procedure documents are available for each assessment. The outcome assessors were trained and the handling of a standard operating procedure short version is mandatory during each data collection period. All variables will be assessed at baseline (prior to randomization) and at study completion.

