### Statistical analysis

The characterization of the sample will be performed by descriptive statistical analysis using measures of central tendency (mean and median) and variability (standard deviation and interquartile range). The normality of the data will be tested by the Shapiro-Wilk test. Intra- and inter-group analyses will be performed before and after the total 12-week intervention period. For both analyses the generalized estimation equations (GEE) will be used. Correlations between peak VO_2_ and study variables – quality of life, functionality, muscle strength, endothelial function, and lean body mass – will be examined by Pearson or Spearman coefficients as appropriate.

In all tests, a significance level of *p* < 0.05 will be adopted. All data will be analyzed using SPSS Statistics for Windows version 20.0 (IBM Corp., Armonk, NY, USA) by the intention-to-treat and protocol methods.

Dropouts (essentially, participants who withdraw consent for continued follow-up) or missing data will be included in the analysis by modern imputation methods.

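### Patients with a cardiovascular event, hospitalisation or severe health event leave the study, so their 12-week primary outcomes go unobserved and must be imputed under an intention-to-treat label

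*Protocol article*

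**What the plan says.** All statements are in the protocol article.

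- **Criteria for discontinuation and safety interventions.** Three situations are described. The investigator may act for safety reasons: "A participant may be discontinued from the study". For any participant, "an incident cardiovascular event, hospitalization, or severe health event during the intervention period are considered criteria to discontinue study participation". For chest pain, disabling dyspnoea or syncope during a session, the wording changes: "the exercise intervention will be interrupted".
- **Outcomes and Data collection.** There are two measurement times: "All variables will be assessed at baseline (prior to randomization) and at study completion". The second falls at 12 weeks: "At the end of the 12-week period, the subject will be re-evaluated". No intermediate assessment is described, and no separate follow-up for patients who have been discontinued.
- **Statistical analysis.** Data are to be analysed "by the intention-to-treat and protocol methods". On incomplete data: "Dropouts (essentially, participants who withdraw consent for continued follow-up) or missing data will be included in the analysis by modern imputation methods". The imputation method is not named.

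**The concern.** An intention-to-treat comparison needs the outcomes of all randomised patients, whether or not they continue the allocated treatment. Here the protocol itself takes some patients out of the study, and it does so because of events after randomisation. In patients with NYHA class II–III heart failure and an ejection fraction of 45% or less, such events plausibly go with lower exercise capacity and worse quality of life, which are the two primary outcomes. The missing values would then be informative, and the account of dropouts in the analysis section does not mention this group.

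The arms need not lose patients equally. Functional training is self-paced with encouragement towards high performance, its safety is a stated secondary objective, and each arm has only 19 patients, so one or two events more on one side is easily possible. The Harms section lists shortness of breath, fatigue and muscular pain, but not the events that trigger removal, so an imbalance might not show in the safety report.

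This differs from leaving an imputation model to a later analysis plan. A later plan can choose a better model, but it cannot recover 12-week values that were never collected.

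**Working it through.** **1. Does the rule end follow-up or only training?** The same section uses two wordings: leaving the study (investigator's discretion; cardiovascular event, hospitalisation or severe health event) and interrupting the exercise (symptoms during a session). Patients with an event fall under the first. With measurements only at baseline and completion, a patient removed in, say, week 5 has no post-baseline peak VO2 or Minnesota score.

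**2. How do these patients enter the analysis?** They are not consent withdrawals, so the description of dropouts does not fit them. They can enter only under the general term for missing data, and so by imputation. This is an inference; the article does not say it of these patients by name.

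**3. The one stated figure nearby.** The Sample size section goes from 16 to 19 per arm (32 to 38 in total) for 20% loss or refusal. 16 × 1.2 = 19.2, so 19 is reproduced by multiplying; dividing gives 16 / 0.8 = 20. The point here does not depend on this step. The 20% is an allowance for loss or refusal, not an event rate.

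**4. Size of the distortion.** Assume that imputation gives event patients the mean of event-free patients in their arm, as a missing-at-random model with little other information would do. Let μ be the event-free mean, p the share with an event, and D the amount in SD by which event patients are truly worse than the imputation predicts.

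- True arm mean: (1 − p) × μ + p × (μ − D) = μ − p × D
- Arm mean after imputation: μ
- Arm mean overstated by: p × D
- Distortion of the difference, functional (F) minus strength (S), with a common D: (pF − pS) × D
- With different deficits: pF × DF − pS × DS

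The documents give neither event shares nor D. The values below are assumptions.

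| Events, F vs S | D = 0.5 | D = 1 | D = 2 |
|---|---|---|---|
| 5% vs 5%, or 20% vs 20% | 0 | 0 | 0 |
| 10% vs 5% | 0.025 | 0.05 | 0.10 |
| 20% vs 5% | 0.075 | 0.15 | 0.30 |
| 1 vs 0 of 19 | 0.026 | 0.053 | 0.105 |
| 2 vs 0 of 19 | 0.053 | 0.105 | 0.211 |

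Entries are in SD. Example: (0.20 − 0.05) × 2 = 0.30. If the strength arm has more events, the sign reverses.

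**The case against.** The strongest reply is that the discontinuation section is loosely worded and follow-up in fact ends only when consent is withdrawn. The section sits under Intervention. The 12-week re-evaluation is stated without exception. The retention section stops telephone calls only for participants who declare withdrawal. The analysis section ties dropout to withdrawal of consent for further follow-up. This shows that the article can be read in a softer way, but it does not displace the plain wording, because the same section uses a different phrase when it means only the exercise. If the softer reading is intended, one sentence saying so settles the matter.

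Second, the imputation model is not given, and a protocol article may leave it to the analysis plan. That stands. The formula above is therefore conditional on a missing-at-random model. The loss of the observed values is not.

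Third, some peak VO2 values would be missing whatever the protocol said, because not every patient can be exercise-tested after an event. That also stands; the gain is mainly in the questionnaires.

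A reader might also infer that the analysis is not intention-to-treat at all, or that the worst outcomes are removed so that the arm with more events gains. The documents do not support this. Missing data are to be included in the analysis, so these patients keep their place in the allocated arm. No outcomes after events are given, and hospitalisation is not limited to heart failure. The direction of bias depends on shares and deficits that are unknown. Nor can a one-arm shift of (k/19) × D for k events be set directly against the difference the trial can detect, since that holds only if the other arm has no events.

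**Conclusion.** The point holds as a mismatch between two sections. The discontinuation rule ends study participation for reasons plausibly related to the outcome, while the analysis section promises intention-to-treat and explains dropout essentially by consent withdrawal. Followed as written, the rule leaves the 12-week primary outcomes of these patients unobserved and to be imputed.

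If the imputation assumes missing at random, the between-arm distortion is about 0.03 to 0.30 SD for event shares of 10% or 20% against 5% and deficits of 0.5 to 2 SD, and zero for equal shares and deficits. For scale, 19 per arm can detect 0.93 SD with an unadjusted two-sided t-test at 5% and 80% power. The upper end of the range would therefore matter, and the lower end would be minor. Neither size nor direction can be derived from the documents. The change should be made because it is cheap and because data not collected cannot be replaced later.

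**What to change.** Reconcile the discontinuation and Statistical analysis sections by separating the end of the exercise programme from the end of follow-up.

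1. Leave the exercise-stopping criteria unchanged.
2. State that every randomised patient who has not withdrawn consent is kept for the planned 12-week assessment: questionnaires from all, and exercise testing where the responsible clinician allows it.
3. Extend the account of dropouts to patients whose training was stopped for an event, and report by arm the events that prevent measurement.
4. Add a sensitivity analysis that does not assume these patients resemble event-free patients, for example by imputing less favourable values over a stated range.

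The cost is a short amendment and a few 12-week assessments in patients who have stopped training. The sample size does not change. Some peak VO2 values will still be missing, which is why items 3 and 4 are needed.
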